## Background

Humeral shaft fractures are associated with a profound temporary (in elderly sometimes even permanent) impairment of independence and quality of life. Fractures of the humeral shaft account for 1-3% of all fractures [1]. The cumulative incidence shows a peak in the working population (14.5/100,000 person years) as well as in the elderly (60/100,000) [1-3].

Humeral shaft fractures can be treated operatively or non-operatively. Operative treatment is mostly performed by intramedullary nailing, plate osteosynthesis, or external fixation. Non-operative immobilization is mostly done with a functional (Sarmiento) brace [4]. Operative and non-operative treatment strategies both have their pros and cons. Operative fracture fixation allows for early mobilization, which may lead to earlier functional recovery and reduced pain. However, surgical complications and fixation failure may occur [5]. Non-operative treatment may be associated with more pain (as the fracture is not stabilized) and discomfort (due to pain and immobilization) in the first weeks and may be associated with a higher malunion risk due to the lack of fracture re-alignment [6,7]. Longer immobilization may delay functional recovery.

Complications of operative and non-operative treatment overlap and data are lacking to determine treatment relatedness. Non-union occurs in 15-30% after operative treatment [5] versus 2-23% after non-operative treatment (for which most patients require secondary surgical treatment) [6,7]. The most feared disabling complication is radial nerve palsy, occurring in 2-17% of all patients [8-10]. A systematic review (n = 4,517 patients) reported an average radial nerve palsy of 11.8%. Although 70% recover spontaneously, the palsy was permanent in 12% of cases accounting for a substantial impairment and costs [9].

Regaining function is extremely important from a patient and societal perspective. From the few retrospective and prospective case series published, each using other outcomes, better functional outcome is expected after operative treatment [8,11-17].

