### Study population

All persons aged 18 years or older presenting to the ED with a humeral shaft fracture (AO type 12A or 12B) are eligible for inclusion [33]. The AO type 12C fractures will be excluded due to their low occurrence rate. Humeral shaft fractures are defined as fractures located in the area between the surgical neck and the area immediately above the supracondylar ridge.

Patients meeting the following inclusion criteria are eligible for enrolment:

1. Adult men or women aged 18 years or older (with no upper age limit)

2. A fracture of the humeral shaft, AO class 12A or 12B (confirmed on X-ray)

3. Operation within 14 days after presentation to the ED (if this is the treatment of choice)

4. Provision of informed consent by patient

If any of the following criteria applies, patients will be excluded:

1. Patients with concomitant injuries affecting treatment and rehabilitation of the affected arm

2. Patients with a humeral fracture treated with an external fixator

3. Patients with a pathological, recurrent or open humeral shaft fracture

4. Patients with neurovascular injuries requiring immediate surgery (excl. radial nerve palsy)

5. Additional traumatic injuries of the affected arm that influence upper extremity function

6. Patients with an impaired upper extremity function (*i.e.*, stiff or painful arm or neurological disorder of the upper limb) prior to the injury

7. Retained hardware around the affected humerus

8. Patients with rheumatoid arthritis

9. Bone disorder which may impair bone healing (excluding osteoporosis)

10. Patients incapable of ensuring follow-up (*e.g.*, no fixed address or cognitive impairment)

11. Insufficient comprehension of the Dutch language to understand the rehabilitation program and other treatment information, as judged by the treating physician of researcher

Exclusion of a patient because of enrolment in another ongoing drug or surgical intervention trial will be left to the discretion of the attending surgeon on a case-by-case basis.

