The Short-Form 36 (SF-36) is a validated multi-purpose, health survey with 36 questions, representing eight health domains that are combined into a physical and a mental component scale [38]. The Physical Component Summary (PCS) combines the health domains physical functioning (PF; 10 items), role limitations due to physical health (RP; 4 items), bodily pain (BP; 2 items), and general health perceptions (GH; 5 items). The Mental Component Summary (MCS) combines the health domains vitality, energy, or fatigue (VT; 4 items), social functioning (SF; 2 items), role limitations due to emotional problems (RE; 3 items), and general mental health (MH; 5 items). Scores ranging from 0 to 100 points are derived for each domain, with lower scores indicating poorer function. These scores will be converted to a norm-based score and compared with the norms for the general population of the United States (1998), in which each scale was scored to have the same average (50 points) and the same standard deviation (10 points).

The EuroQol-5D is a validated questionnaire for measuring health-related quality of life [39,40]. Its use is recommended for assessing quality of life in trauma patients, especially for economic assessments [41,42]. The EQ-5D descriptive system consists of five dimensions of health (mobility, self-care, usual activities, pain/discomfort and anxiety/depression). Scores are converted to a utility score ranging from zero to one, with lower scores indicating poorer quality of life. The EQ VAS records the respondents self-rated health status on a vertical (0–100) visual analog scale.

The cost-effectiveness analysis will be performed from a societal perspective and will include costs for health care and production losses. Patients will be asked to complete a custom-made questionnaire that contains detailed information on both items. Health care costs will include general practice care, medical specialist care, nursing care, physical therapy, hospitalization, medication, home care, and other costs directly associated with diagnosis, treatment, and rehabilitation.

In addition to the outcome variables mentioned above, the following data will be collected:

a) Intrinsic variables (baseline data): age, gender, American Society of Anesthesiologists’ ASA classification, tobacco consumption, alcohol consumption, comorbidities (including osteoporosis), dominant side, and medication use.

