### Study procedures

Clinical evaluation will occur at two weeks (7–21 days window), six weeks (4–8 weeks window), three months (11–15 weeks window), six months (6–7 months window), and 12 months (12–14 months window) after start of treatment [Table 1]. These visits are standard of care for the targeted patient group. At each follow-up visit, the research coordinator or research assistant will ascertain patient status (*i.e.*, adverse events/complications, secondary interventions, etcetera, and will verify information within medical records).

**Table 1 T1:** Schedule of events

**Radiographs & events**	**Screening**	**Enrolment**	**Baseline**	**Post**	**2 weeks**	**6 weeks**	**3 months**	**6 months**	**12 months**
				**surgery**	**(7–21 d)**	**(4–8 we)**	**(11–15 we)**	**(6–7 mo)**	**12-14 mo)**
X-ray	X						X^1^	X^1^	X^1^
Screening	X								
Informed consent		X							
Baseline data			X						
Surgical report form				X					
DASH					X	X	X	X	X
Pain (VAS)					X	X	X	X	X
SF-36					X	X	X	X	X
EQ-5D					X	X	X	X	X
Clinic FU					X	X	X	X	X
Range of motion					X	X	X	X	X
Secondary interventions					X	X	X	X	X
Complications					X	X	X	X	X
Health care consumption					X	X	X	X	X
ADL/work resumption					X	X	X	X	X
Physical therapy					X	X	X	X	X
Constant score						X	X	X	X
Early withdrawal					*	*	*	*	*

^1^X-rays will be taken according to local protocol; all X-rays after three months will be analyzed. The six-month X-ray is needed for assessing fracture healing. If no signs of healing are seen at six months, the 12-month X-ray is also required.

*Only at time of withdrawal.

At each follow-up visit, the range of motion of the shoulder and elbow will be measured using a goniometer by a physician or research assistant. In addition, patients will be asked to complete the questionnaires relating to disability (DASH score including optional modules), pain (VAS), health-related quality of life (SF-36, EQ-5D), health care consumption and production loss. From six weeks onwards, the research coordinator or research assistant will determine the Constant score.

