For the secondary analysis we will develop a propensity score model as published before [43,44]. Characteristics including fracture type, age, gender, mechanism of injury, dominance, and activity levels will be included in this model; the resulting propensity score represents the chance of being operated. Next, the logit of the propensity score will be used in order to match each patient receiving operative treatment with one or more patients receiving non-operative treatment. The effect of operative treatment will be analyzed with linear or ordinal logistic mixed effects regression analysis taking the matched-pairs design into account. In the matched cohort, comparisons will be performed using a McNemar test (for categorical data), and a paired sample t test (parametric, continuous data) or a Wilcoxon signed rank test.

The economic evaluation will be performed from a societal perspective. Costs will be measured in accordance with Dutch guidelines for economic evaluations, using standard cost prices as published by Hakkaart-Van Rooijen et al. where possible [45]; effects will be discounted at a rate of 1.5% and costs at 4% per year [45]. The incremental cost-effectiveness ratio (ICER) of operative versus non-operative treatment will be expressed in a cost-utility ratio (*i.e.*, cost per QALY) using the EQ-5D utility score as effect measure. Uncertainty around this ratio will be presented using confidence ellipses on the cost-effectiveness plane and acceptability curves.

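### No baseline or recalled pre-injury EQ-5D is scheduled, so the cost-per-QALY analysis must assume utility over the first one to three weeks and has no pre-treatment utility for adjustment

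*Protocol article*

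**What the plan says.** The economic part of Statistical analysis in the protocol article plans a cost per QALY for operative versus non-operative treatment, "using the EQ-5D utility score as effect measure".

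Study procedures ties the questionnaires to the follow-up visits, at which "patients will be asked to complete the questionnaires relating to disability (DASH score including optional modules), pain (VAS), health-related quality of life (SF-36, EQ-5D" and the resource-use items. The visits are set out as follows: "Clinical evaluation will occur at two weeks (7–21 days window), six weeks (4–8 weeks window), three months (11–15 weeks window", then six months, and finally "12 months (12–14 months window) after start of treatment". The EQ-5D row of Table 1 agrees. It is marked at all five follow-up visits and blank under Screening, Enrolment, Baseline and Post surgery.

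Outcome measures lists the extra data to be collected, beginning with "Intrinsic variables (baseline data): age, gender" and going on to ASA class, smoking, alcohol, comorbidities, dominance and medication. Injury and intervention variables follow. None is a utility, a quality-of-life score or a recalled pre-injury state.

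Two other statements bear on the point. Background expects non-operative treatment to bring more pain, and "discomfort (due to pain and immobilization) in the first weeks". Study population requires, for operated patients, "Operation within 14 days after presentation to the ED (if this is the treatment of choice".

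**The concern.** A QALY is the area under the utility curve from time zero. Here the first point on the curve comes one to three weeks after treatment starts, so the analyst has to supply the starting value. The operation, much of the hospital stay and the first days of immobilisation fall in that stretch. Their costs are counted, but the utility that goes with them is not measured.

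The second consequence concerns confounding. Treatment is chosen by the surgeon, and Background reports that surgeons say they are guided by patient characteristics and expected physical demands. A pre-treatment utility would be the natural covariate in the QALY comparison. The two-week score cannot take that role, because treatment has already acted on it.

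The assessment schedule is printed in full, with a Baseline column, so this is a stated choice and not a detail left to another document. An analysis plan can state an assumption about the start of the curve, but it cannot supply data that were not collected.

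**Working it through.** The protocol gives no QALY figure to reproduce and no utility values. All utilities below are assumptions; the timings come from the protocol.

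**1. Length of the unmeasured stretch.** The first EQ-5D falls on day 7 to 21 after start of treatment, nominally day 14.
- 7/365 = 1.9%, 14/365 = 3.8% and 21/365 = 5.8% of the year.
- Surgery may follow up to 14 days after presentation. If start of treatment means the operation, the first EQ-5D in an operated patient can come 14 + 21 = 35 days after presentation: 35/365 = 9.6%.
- If non-operative treatment starts at presentation, its limit is 21 days. The unmeasured time since injury can therefore differ between the groups.

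**2. Contribution of the unknown start.** With utility moving linearly to its first measured value, a between-group starting difference d0 adds d0 × (t1/365)/2 QALY, where t1 is the day of the first EQ-5D. An error of equal size in both groups cancels.

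| t1 | d0 = 0.1 | d0 = 0.3 |
|---|---|---|
| 14 days | 0.0019 | 0.0058 |
| 21 days | 0.0029 | 0.0086 |
| 35 days | 0.0048 | 0.0144 |

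For day 14 to 21 the range is 0.002 to 0.009 QALY.

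**3. Against a plausible gain.** Assume a utility advantage of 0.05 to 0.10 for a quarter of a year: 0.05 × 0.25 = 0.0125 and 0.10 × 0.25 = 0.025 QALY. The first interval is then between 0.0019/0.025 = 8% and 0.0086/0.0125 = 69% of the gain.

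**4. Whole-year illustration.** Take visits at days 14, 42, 91, 182 and 365, with assumed differences favouring surgery.

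*Larger scenario:* 0.10, 0.10, 0.05, 0, 0.
- Measured part: (28 × 0.10 + 49 × 0.075 + 91 × 0.025)/365 = 8.75/365 = 0.024 QALY.
- First interval: 14 × (d0 + 0.10)/2 utility-days, which is −1.40 at d0 = −0.3 and +2.80 at d0 = +0.3.
- Total: 7.35/365 = 0.020 to 11.55/365 = 0.032, a ratio of 1.6.

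*Smaller scenario:* 0.05, 0.05, 0.03, 0, 0.
- Measured part: (28 × 0.05 + 49 × 0.04 + 91 × 0.015)/365 = 4.725/365 = 0.013 QALY.
- First interval: −1.75 to +2.45 utility-days.
- Total: 2.975/365 = 0.008 to 7.175/365 = 0.020, a ratio of 2.4.

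With the cost difference held fixed, the ICER changes by the same factors.

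**5. Can the sign change?** A total of zero needs d0 = −0.05 − 2 × 4.725/14 = −0.725 in the smaller scenario and −0.10 − 2 × 8.75/14 = −1.35 in the larger. The first lies far beyond the assumed range. The second is impossible on the protocol's zero-to-one utility scale.

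**The case against.** The other side has real weight.

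- **Most of early recovery is measured.** A reader might infer that the schedule misses the period in which the treatments are expected to differ most. The protocol does not say so. It speaks of the first weeks in general terms, and its only quantified difference (DASH 16 versus 10 in Sample size calculation) is at three months. Usual non-operative care is described as 1–2 weeks of splint or cast and then 4–6 weeks of brace, so the two- and six-week visits fall within or near it. This stands.
- **The gap need not swamp the effect.** Applying a 0.3 error at full height over 21 days gives 0.3 × 21/365 = 0.017 QALY, more than the smaller assumed gain of 0.0125. A reader might conclude that the first interval can exceed the whole effect. That treats the error as constant up to the day on which utility is measured; the trapezoid rule halves it. The assumed gain also leaves out any effect of non-union, nerve palsy or re-intervention after three months.
- **Adjustment is planned.** A reader might take an unadjusted pre-injury difference of 0.05 over a year (0.05 QALY) as the likely bias. The protocol plans a covariate-adjusted mixed model for EQ-5D and propensity matching that includes age, mechanism and activity levels. It excludes prior arm impairment, and its retrospective data showed no obvious differences in patient characteristics. So that figure is not supported as an expected bias. What remains is that none of these variables is a utility, and that the economic section does not tie the adjustment to the QALY contrast.
- **The starting assumption belongs in an analysis plan.** This is true of the assumption, and the protocol does not commit to any biased method such as carrying the two-week value back. It is not true of the data collection.
- **Cost-effectiveness is a secondary outcome.** The primary DASH analysis is untouched.

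**Conclusion.** The point holds in limited form. No EQ-5D is scheduled before or at the start of treatment, so the QALY curve needs an assumed start, and the non-randomised QALY comparison lacks the covariate best suited to it. Later visits cannot recover either.

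The size is modest: 0.002 to 0.009 QALY for an assumed between-group starting difference of 0.1 to 0.3 and a first visit on day 14 to 21. In the illustrations this moved a small gain by a factor of 1.6 to 2.4 across starting differences of −0.3 to +0.3, without changing its sign. The planned confidence ellipses and acceptability curves reflect sampling uncertainty and would not by themselves show this dependence on an assumption. Imbalance in pre-injury utility is plausible but not demonstrated.

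The change is worth making because it is cheap. It does not threaten the primary objective.

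**What to change.** Add EQ-5D to the Enrolment/Baseline column of Table 1, completed at the existing inclusion contact (emergency department or first outpatient visit) in two forms:

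- a recalled score for the state before the injury, used as a covariate in the QALY comparison and as a candidate variable for the propensity score;
- a dated current-state score, used to start the QALY curve.

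Some patients are included at the first outpatient visit, when immobilisation may already have begun, so a pre-treatment current-state score will not exist for everyone. The date shows for whom it does. For those patients, and for those enrolled since October 2012 without either score, use one common starting-utility assumption in both groups. Vary it in a sensitivity analysis, including with different values by group.

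The cost is two short forms at a contact that already takes place and one change to the schedule table. The drawbacks are recall error in the pre-injury score and missing values for earlier patients. At the expected 10 inclusions per month, 400 patients take about 40 months, so an early change would still reach many of them.

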### Ethical considerations

The study will be conducted according to the principles of the Declaration of Helsinki (59th World Medical Association General Assembly, Seoul, October 2008). This study has been given a waiver of consent by the medical research ethics committee (MREC); in Dutch: Medisch Ethische Toetsings Commissie (METC). Following review of the protocol, the MREC concluded that this study is not subject to the Medical Research Involving Human Subjects Act (WMO). They concluded that the study is a medical/scientific research, but no patients are subjected to procedures or are required to follow rules of behavior. Consequently, the statutory obligation to provide insurance for subjects participating in medical research (article 7, Subsection 6 of the WMO and Medical Research (Human Subjects) Compulsory Insurance Decree of 23 June 2003) was also waived.

The MREC Erasmus MC (Rotterdam, The Netherlands) acts as central ethics committee for this trial (reference number MEC-2012-296). Approval has been obtained from the local hospital boards in all participating centers.

## Discussion

The HUMMER trial will study outcome after operative versus non-operative treatment of humeral shaft fractures. Operative treatment is expected to result in earlier recovery than non-operative treatment. Earlier functional recovery will result in a better quality of life of patients, earlier work and ADL resumption, a higher level of independency, and less health care needs. Although costs for initial treatment will be higher in the operative group (due to surgery), we hypothesize that costs will be saved by less health care needs during the recovery process and less productivity loss. Despite higher initial costs, we expect that primary surgery will be more cost-effective. To the best of our knowledge, this is the first high-quality multicenter prospective observational study that will look at patient, medical and societal perspective in patients with a humeral shaft fracture.

Thirty hospitals in the Netherlands will participate. Inclusion of patients has started October 01, 2012 and the expectation is to include 10 patients per month. With a follow-up of one year the presentation of data will be expected in the beginning of 2016.

## Abbreviations

ADL: Activities of daily living; AO: Arbeitsgemeinschaft für Osteosynthesefragen (German for “Association for the Study of Internal Fixation”); ASA: American Society of Anesthesiologists; BP: Bodily pain; DASH: Disabilities of the arm, shoulder and hand score; ED: Emergency Department; EQ-5D: EuroQol-5D; GH: General Health perception; HR-QoL: Health-related quality of life; MCS: Mental component summary; MH: General mental health; MREC: Medical Research Ethics Committee; NTR: Netherlands Trial Registry (in Dutch: Nederlands Trial Register); PCS: Physical component summary; PF: Physical functioning; QALY: Quality-adjusted life years; QoL: Quality of life; RCT: Randomized controlled trial; RE: Role limitations due to emotional problems; ROM: Range of motion; RP: Role limitations due to physical health; SD: Standard deviation; SF: Social functioning; SF-36: Short form-36; SPSS: Statistical package for the Social Sciences; STROBE: Strengthening the reporting of observational studies in Epidemiology guidelines; VAS: Visual analog scale; VT: Vitality, energy, or fatigue.
